## Abstract

**Introduction:**

Advances in cystic fibrosis (CF) care have coincided with an increasing prevalence of excess body weight in this population, which may contribute to cardiometabolic and respiratory morbidity. However, evidence to guide intentional weight loss in this population is limited and safety concerns remain due to the established positive association between body weight and lung function. Delivering weight-loss interventions in CF is likely to be complex because of CF-specific factors, high treatment burden and embedded dietary advice focused on high-energy, high-fat diets for weight gain. To inform the design of a future definitive randomised controlled trial (RCT), we plan to test the feasibility, acceptability and safety of a dietitian supported weight-loss intervention compared with routine care.

**Methods and analysis:**

This multicentre feasibility RCT with an embedded qualitative study, will recruit 30 adults with CF and body mass index ≥27 kg/m^2^ from four UK specialist centres. Participants will be randomised 2:1 to the EASE-CF intervention or routine dietetic consultations, with follow-up over 24 weeks. The remotely delivered, theory-informed intervention combines structured dietary energy restriction, meal replacements and behavioural support from specialist CF dietitians. Participants randomised to routine care will continue to receive standard CF dietetic input. The primary objective is to assess the feasibility of progression to a definitive RCT based on pre-specified criteria on recruitment, engagement, adherence, retention and safety. Assessment of intervention acceptability and fidelity will be explored through process measures and qualitative interviews with participants and healthcare professionals. Exploratory outcomes include changes in body weight and composition, lung function, quality of life, physical function and metabolic markers.

**Ethics and dissemination:**

Ethical approval has been granted by the National Research Ethics Service South Central B Research Ethics Committee (ref: 25/SC/0323). Findings will be disseminated through stakeholder engagement, conference presentations and publication in open-access, peer-reviewed journals.

**Trial registration number:**

ISRCTN17298282.

WHAT IS ALREADY KNOWN ON THIS TOPICA growing proportion of adults with cystic fibrosis (CFNor) now live with overweight or obesity. However, structured weight reduction strategies have not been formally evaluated in CF, and clinicians lack evidence to guide safe management of excess weight in this context.WHAT THIS STUDY ADDSThis study evaluates the feasibility of delivering a specialist dietitian-led weight loss intervention for adults with CF and excess weight, including recruitment, retention, engagement and adherence. An embedded qualitative process evaluation will examine intervention acceptability, fidelity and implementation challenges.HOW THIS STUDY MIGHT AFFECT RESEARCH, PRACTICE OR POLICYRemote delivery of the theory-informed intervention reflects current clinical practice, reduces participant burden and supports scalability within routine CF care. As a feasibility study, it is not powered to assess clinical effectiveness. Findings will inform the design of a definitive randomised controlled trial.

## Introduction

 Cystic fibrosis (CF) is a rare, genetic, life-limiting condition characterised by progressive lung disease and multisystem involvement, requiring complex multidisciplinary care.^1^ Advances in treatment have improved survival, with UK registry data showing the median life expectancy increasing from 36 years in 2013 to an estimated 64 years in 2024.^2^ These gains are largely attributable to the introduction of CF transmembrane conductance regulator (CFTR) modulators, which improve the function of the CFTR protein and are prescribed according to genotype.^3^ On average, CFTR modulator therapy is associated with improved lung function, reduced frequency of infective pulmonary exacerbations and enhanced quality of life.^4^ Consequently, CF services are now adapting to the needs of a heterogeneous and ageing adult population.^5^

Improved survival has been accompanied by important shifts in nutritional status. Historically, CF was associated with undernutrition, and dietary guidance promoted high-energy, high-fat intake (the ‘CF legacy diet’).^6^ However, excess weight (body mass index (BMI) ≥25 kg/m²) now affects over 40% of UK adults with CF (54% of those aged >50 years), three times the prevalence of underweight, making this approach unsuitable for many and potentially contributing to further weight gain.^2^

The mechanisms underlying weight gain on CFTR modulators include reduced total energy expenditure, improved appetite and enhanced nutrient absorption due to changes in gut function.^7^ Although the prevalence of overweight and obesity in people with CF remains lower than in the general population, this trend is concerning because people with CF have an increased risk of cardiovascular disease and gastrointestinal cancers compared with the general population, and excess weight may further compound these risks.^8
9^ Emerging evidence also suggests that excess weight may adversely affect respiratory health, including lung function decline.^10
11^

Weight loss may confer benefits similar to those observed in other chronic conditions.^12^ However, there is limited trial-based CF-specific evidence examining the rate, magnitude or safety of weight reduction, with concerns including unintended loss of muscle mass and deterioration in lung function. Published case reports describing bariatric surgery or GLP-1 receptor agonist therapy for weight loss in people with CF have raised concerns about physical fitness and function that warrant further detailed evaluation.^13–15^

Achieving intentional weight loss in people with CF presents specific challenges. Long-standing guidance for the ‘CF legacy diet’ may create cognitive dissonance when energy restriction is advised. Consequently, individuals with CF may need to modify ingrained eating habits, often established in childhood and reinforced during adulthood by clinicians and their social, cultural and economic environments.^16^ In addition, CF-specific complications including pancreatic insufficiency, gastrointestinal complications and CF-related diabetes need to be considered when dietary changes are introduced. The high daily clinical treatment burden may also limit engagement with structured weight-loss interventions. Collectively, these factors suggest that weight-loss interventions in CF may need to target the behavioural processes required to establish and sustain dietary change.

Evidence from weight-loss trials conducted in other chronic disease populations can inform intervention design, but these approaches require testing in a CF-specific context. In the UK, dietetic support is embedded within CF services, and both patients and clinicians view dietitian supported weight loss support as appropriate. However, uncertainty remains regarding the feasibility, acceptability and optimal delivery of weight-loss interventions within routine CF care.^16–18^

Despite the increasing prevalence of excess weight in CF, no clinical trials have evaluated intentional weight loss in this population, and current CF nutrition guidelines provide no structured recommendations for assessment or management of overweight and obesity.^19–21^ This reflects ongoing clinical equipoise, limited CF-specific evidence and practical constraints within CF teams, highlighting the need for feasibility testing prior to a definitive trial. The importance of addressing this evidence gap is further highlighted by the 2023 James Lind Alliance Priority Setting Partnership that identified the question “How can overweight and obesity be effectively managed in people with CF?” within its fourth highest-ranked research priority of “How do we manage an ageing population with CF?”.^22^

In response to these uncertainties, we developed a theory-informed weight-loss intervention with input from CF clinicians and people with lived experience of CF and excess weight. The intervention combines structured dietary energy restriction, including meal replacements and ready-prepared meals, with behavioural support delivered by specialist CF dietitians.

We have planned a randomised controlled feasibility trial to assess whether a definitive trial is warranted. Primary feasibility outcomes include recruitment and willingness to be randomised, engagement and adherence to the intervention, retention, acceptability of the intervention and study procedures, and safety, including potential effects on CF-specific health outcomes such as lung function. Qualitative interviews with participants and clinicians will explore acceptability and implementation processes to inform optimisation of the intervention and trial design.^23^

## Methods and analysis

### Study design and setting

This feasibility study is a randomised controlled trial (RCT) in adults with CF and a BMI ≥27 kg/m^2^, recruited from specialist CF centres in the UK. Each participant will be enrolled for 24 weeks from randomisation to final follow-up and will attend four study assessments. Due to the nature of the intervention, it will not be possible to blind the participants or clinicians delivering the intervention.

### Recruitment

Participants will be recruited from four UK CF centres over a period of 12 months; centres were identified via an expression of interest and feasibility assessment coordinated by the UK CF Trust Clinical Trials Accelerator Platform team. Sites were selected based on dietetic and research staff capacity and geographical representation. Established patient cohorts enable database screening to identify potentially eligible participants. Reasons for declining participation will be recorded using a predefined list in the screening log to inform assessment of recruitment feasibility.

### Inclusion criteria

Key inclusion criteria include:

Aged ≥18 years.BMI ≥27 kg/m^2^ (or BMI ≥25 kg/m^2^ for people of Black, Asian or minority ethnic origin).^24^ The threshold of ≥27 kg/m² was selected to minimise the risk of participants reducing their weight below recommended CF BMI targets (≥23 kg/m²) during the intervention weight loss, and to avoid inclusion of individuals with mild overweight who may be more likely to fall below these thresholds. This cut-off also aligns with CF nutritional guidelines that define overweight at BMI ≥27 kg/m²).^19^Access to the internet and an internet-enabled device (smartphone, tablet, computer – a device can be provided if required).Established diagnosis of CF including those who have previously received a lung or liver transplant.Forced expiratory volume (FEV1) ≥25% predicted recorded in the last 6 months.

### Exclusion criteria

Key exclusion criteria include:

Currently participating in a structured weight-loss intervention or ≥10% self‐reported weight loss in the 6 months before the screening visit.Documented decompensated liver disease.Documented stage 4–5 chronic kidney disease.Actively using enteral feeding.Pregnancy or breastfeeding.

### Study procedures and participant flow

All study visits will be conducted remotely via Microsoft Teams or equivalent to minimise participant burden and assess the feasibility of home measurements. The baseline assessment will last approximately 60 min and follow-up assessments 15–20 min. Technical support to help participants access Microsoft Teams will be provided where required. Informed consent will be obtained remotely by a delegated member of the local research team. Eligibility will then be confirmed, and baseline assessments will be conducted using home monitoring equipment posted to the participant prior to the baseline assessment and a returned blood sample kit. Once all baseline measurements are finalised, participants will be randomised. Those allocated to the routine care group will follow the local standard care pathway attending their CF appointments. Participants in the intervention group will attend an initial dietetic consultation to receive intervention materials and commence the intervention. Remote assessments will take place at 4, 12 and 24 weeks. Intervention participants will participate in a qualitative interview at 12 or 24 weeks, and routine care participants will have a qualitative interview at 24 weeks. Weight and lung function data will be obtained from routine clinical records, including data collected as part of standard care and reported to the UK CF Registry, for up to 2 years post-study. Participant flow is shown in figure 1.

**Figure 1 F1:**
[figure not shown]
Participant flow through the study. CF, cystic fibrosis; EQ-5D-5L, EuroQol 5-dimension 5-level.

### Sample size

The study aims to recruit 30 participants (20 intervention, 10 routine care). As this is a feasibility study, it is not powered to detect a clinically or statistically significant difference between groups.^25^ The sample size was not arrived at using a statistical method but was informed by guidance to estimate key feasibility criteria with sufficient precision to inform progression decisions and the design of a definitive trial.^26^ The 2:1 allocation ratio allows greater experience of the intervention while retaining a comparator group to assess feasibility processes.

### Randomisation

All eligible and consented participants will be randomised 2:1 into the intervention group or routine care using a random permuted block design with blocks of 3 and 6, stratified by presence of CF-related diabetes (yes/no) and age (> or ≤40 years). A researcher independent of the study will generate the allocation sequence using the Sealed Envelope website,^27^ and a member of the local research team will enter the participant details into the randomisation system (Sealed Envelope) but will not have access to the allocation sequence, ensuring allocation concealment. The system will then automatically allocate the participant. Participants will then be informed of their allocation by the local research team. Blinding of participants and dietitians is not possible due to the nature of the intervention; however, risk of bias will be reduced through objective outcomes and standardised data collection.

### Intervention: the EASE-CF programme

EASE-CF is a structured weight-loss programme delivered by a specialist CF dietitian to support adults with CF and excess weight to achieve weight loss of 5%–10% over a 24 week period. The intervention combines structured energy restriction (including a meal replacement product and a portion-controlled ready-prepared meal), individualised goal setting and accountability to a dietitian to promote dietary behaviour change, habit formation and increased self-efficacy.

As, to our knowledge, no previous trials of weight-loss programmes for people with CF have been conducted, the intervention was informed by evidence from other chronic health conditions, relevant study protocols and CF clinician input, including a previous qualitative study exploring CF clinicians’ views on this topic^16^ and a survey of current dietetic practice for overweight and obesity.^17^ A group of people with lived experience of CF and excess weight also helped to shape the research question and inform the mode, delivery and length of the intervention.

The programme includes an initial 60 min consultation to assess dietary patterns and social circumstances, introduce the programme and establish personalised goals, followed by weekly 20 min video consultations to review progress, support self-monitoring of weight, reinforce behaviour change strategies, address barriers, provide accountability and facilitate action planning. The frequency of sessions may be reduced to fortnightly, based on mutual agreement between the dietitian and the participant if the participant is progressing sufficiently towards their weight loss target. Participants continue routine CF dietetic care as these include assessment of other clinical issues not included in the EASE-CF programme. Dietitians delivering the intervention are registered dietitians working within specialist CF services. All study dietitians receive a 2-hour study-specific training session prior to delivering the intervention covering the intervention protocol, behaviour change components and delivery procedures, together with a detailed programme manual and access to central support where required. The dietary component comprises three eating occasions per day (~1300 kcal/day). This standardised prescription was selected to maximise intervention fidelity and simplify delivery within this feasibility study. Participants are monitored throughout the intervention, and dietary adjustments may be made where necessary based on weight loss progress, tolerability and clinical considerations. Each day participants will be asked to consume: (1) A meal replacement product (shake/porridge of 200 kcal, Habitual Healthcare), (2) A portion-controlled high-protein ready meal of up to 600 kcal (Frive) and (3) An additional meal chosen by the participant based on dietitian’s advice for healthful eating. Water or no/low-calorie drinks are advised, with up to two snacks (one high-protein energy-restricted snack and one portion of fruit). The meal replacement products and ready meals are purchased using study funding and provided to participants free of charge. The manufacturers have no role in the study design, data collection, analysis, interpretation or publication of results.

Disordered eating behaviours may be present in people with CF.^28^ Although concerns have been raised regarding the potential for intentional weight loss to exacerbate these behaviours, evidence from systematic reviews and RCTs in other populations with overweight and obesity suggests that structured behavioural weight management interventions do not worsen, and may improve, disordered eating symptoms.^29–31^ The development of this intervention was informed by behaviour change theory, including the Capability, Opportunity and Motivation – Behaviour model, Theoretical Domains Framework and OxFAB taxonomy.^32–34^ Behaviour change techniques targeted psychological capability (knowledge, skills and behavioural regulation), social and physical opportunity (environmental restructuring, social support) and reflective motivation (beliefs, goals and reinforcement). Habit theory was incorporated to support disruption of established cue-behaviour associations and formation of new habits.^35^ Key components include dietitian-led support to maintain motivation and address barriers, guidance on managing lapses and social situations, realistic goal setting with regular self-weighing and provision of a summary booklet and self-selected meal options tailored to participants’ socioeconomic circumstances. The intervention development process will be reported separately.

### Comparator

Participants allocated to the routine care will see a specialist CF dietitian as part of their multidisciplinary care, typically every 3 months, which is the standard of care in the UK.^36^ The dietitian may provide advice and support regarding weight management and behavioural changes if they feel it is required. Current clinical guidelines for people with CF recommend no intervention beyond healthful eating advice for those with overweight or obesity.^19–21^ To incentivise trial participation, the routine care group participants will be offered a one-off 30 min weight-loss consultation with a specialist CF dietitian at the end of the study.

### Schedule of study events

Table 1 provides a schedule of study events.

**Table 1 T1:** Schedule of study events

Procedures	Assessments				6 months after last study visit	Up to 2 years after last study visit
	0 weeks	4 weeks	12 weeks	24 weeks		
	Screening/ baseline	Assessment 1	Assessment 2	Assessment 3		
Informed consent	x					
Eligibility assessment	x					
Demographic questionnaire	x					
Medical history	x					
Concomitant medications	x	x	x	x		
Randomisation	x					
EQ-5D-5L questionnaire	x			x		
AWESCORE questionnaire	x			x		
Weight and fat/fat-free mass	x	x	x	x		
Height	x					
Blood pressure	x			x		
Five times sit-to-stand	x	x	x	x		
Lung function	x	x	x	x		
Lipid profile	x			x		
HbA1c	x			x		
Adverse events assessments	x	x	x	x		
Qualitative interview with participants			x	x		
Qualitative interviews with staff				x		
Feedback questionnaire end of trial (all participants)				x		
Feedback questionnaire end of trial (intervention participants)				x		
Fidelity of intervention delivery		x	x	x		
Additional interview with intervention participants 6 months after the last visit (optional)					x	
Follow-up through medical notes						x

EQ-5D-5L, EuroQol 5-dimension 5-level.

### Baseline data collection

Participants will be asked to self-report their age, sex and ethnicity, relevant medical history, and all current medications, including CFTR modulators and corticosteroids.

### Physical measurements

All assessments will be conducted during a video call to allow researcher guidance. Height will be obtained from medical records or self-reported if unavailable. Participants will measure body weight barefoot and in light clothing using a calibrated digital scale and body composition (fat-free mass and fat mass) using a bioelectrical impedance analyser (BC-730 Tanita, Japan). Participants will be provided with standardised instructions to undertake measurements after voiding and under consistent conditions where possible, including in similar clothing. Body composition measurements will be considered exploratory and interpreted with appropriate caution given the known limitations of bioelectrical impedance analysis. Physical function will be assessed using the 5-times sit-to-stand test.^37^ Participants will measure their blood pressure at home using a validated monitor (Omron 10, Japan) following standard blood pressure measurement guidance.^38^ Spirometry will be performed according to British Thoracic Society guidelines^39^ using a home spirometer (MIR Spirobank Smart, Italy). Blood sample HbA1c and lipid profile will be assessed at baseline and 24 weeks using a home finger-prick blood sampling kit that participants will post to an established laboratory provider (Medichecks, UK). Where available, results obtained at the CF centre within 1 month of the baseline or 24-week visit will be used.

### Questionnaires

At baseline and end of study, the participants will be asked to complete the following health-related quality of life questionnaires. The European Quality of Life Five Dimension questionnaire and subscale (EQ-5D-5L)^40^ and the AWESCORE, a validated 10-item CF-specific quality of life instrument.^41^ At study completion, participants will complete a questionnaire to evaluate the acceptability of both the intervention and the study procedures.

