### Outcomes

#### Primary feasibility outcomes

The primary objective of this study is to assess the feasibility of progression to a definitive RCT. The following progression criteria will determine whether to proceed to a full RCT without changes (green), proceed with amendments (amber) or not proceed (red) (table 2).

**Table 2 T2:** Progression criteria for feasibility outcomes

Criterion	Measure	Green (progress)	Amber (progress with modifications)	Red (stop – do not proceed to definitive trial)
Recruitment	1a Rate (*n* of patients per site per month)	≥0.6	0.35–0.59	≤0.35
Recruitment	1b Total *N* participants recruited	≥30	16–29 (consider adding sites)	15
Engagement	Proportion of participants who attended ten or more sessions during the 24 weeks (60% of sessions) and at least one of the last three sessions.	≥60%	36%–59% (consider modifying based on process evaluation)	≤35%
Adherence	Proportion of participants in the intervention group with ≥5% wt loss at 12 weeks	≥50%	36%–49%	≤35%
Retention	Proportion of randomised participants completing a 24-week follow-up visit	≥75%	51%–74%	≤50%
Safety	Safety profile	Adjudicated by the Study Steering Committee, based on AE and SAE in the intervention arm which are related and unexpected		

AE, adverse event; SAE, serious AE.

**Recruitment rate per month and overall recruitment:** assessed using the number of sites open, the total number of participants recruited, and the number of participants recruited per site.**Engagement rate:** assessed using the proportion of participants who attended ten or more sessions during the 24 weeks (60% of sessions), inclusive of at least one of the last three sessions.**Adherence rate:** assessed using the proportion of intervention participants with ≥5% wt loss at 12 weeks. The ≥5% wt loss threshold at 12 weeks reflects a clinically meaningful benchmark commonly used in weight management studies and provides an early signal of intervention response. Additional data will include attendance at scheduled dietetic appointments, self-reported adherence to the meal replacement/provided meals components and ordering data.**Retention rate:** assessed using the proportion of randomised participants completing a 24-week follow-up visit measured using data documented in the study notes at one time point.**Safety profile:** assessed using adverse events and serious adverse events in the intervention arm that are related and unexpected.

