#### Process measures

The following process measures will be collected to inform any required changes to the intervention or trial design:

Participant experience, assessed via end-of-trial questionnaires.Control group contamination, through qualitative interviews and end-of-study questionnaires, including assessment of whether routine care participants adopted weight loss strategies consistent with the intervention.Fidelity of delivery, assessed by JS reviewing recorded consultations against the intervention manual checklist.

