## Qualitative sub-study

All intervention participants will be offered the option to participate in semi-structured qualitative interviews at 12 or 24 weeks and all routine care participants at 24 weeks. These interviews will explore their acceptability of the intervention, overall trial experience, explore barriers and facilitators to adherence, and identify suggestions that could refine the intervention and trial should it progress to a full RCT. Interviews will also explore participants’ experiences of dietary change, including any psychological or social impacts related to eating behaviours, weight and body image. Participants will have the option to consent to be invited to participate in an additional interview 6 months after the end of their active study participation to provide further data on their experience following completion of the study.

Semi-structured interviews with 10 clinical staff involved in delivering the intervention will explore perceived barriers and facilitators to recruitment, delivery and potential integration of the intervention into routine clinical practice.

All interviews will be conducted by JS, a CF dietitian and developer of the intervention, who will not be routinely involved in intervention delivery or participants’ routine clinical care. Participants will be reassured that their responses will not affect their clinical care. Interviews will last approximately 30 minutes and be audio and video-recorded, transcribed verbatim and analysed using framework analysis, with researcher reflexivity considered throughout the analysis.^45^

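### Acceptability is measured only at week 24 and at optional week-12 or week-24 interviews, so the questionnaire results are likely to over-represent participants who stay

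*Protocol article*

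**What the plan says.** In the protocol article, the Introduction's list of primary feasibility outcomes includes "retention, acceptability of the intervention and study procedures, and safety". The direct participant measures are these:

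- **Questionnaire.** "At study completion, participants will complete a questionnaire to evaluate the acceptability of both the intervention and the study procedures" (Questionnaires). Table 1 has one feedback questionnaire for all participants and one for intervention participants, both marked at 24 weeks only. The Process measures list has "Participant experience, assessed via end-of-trial questionnaires".
- **Interviews.** "All intervention participants will be offered the option to participate in semi-structured qualitative interviews at 12 or 24 weeks" (Qualitative sub-study); routine care participants are offered theirs at 24 weeks. On content: "These interviews will explore their acceptability of the intervention, overall trial experience, explore barriers and facilitators to adherence". A further optional interview comes six months after active participation ends.

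The Abstract places the topic outside the progression criteria: "Assessment of intervention acceptability and fidelity will be explored through process measures and qualitative interviews with participants and healthcare professionals". Table 2 covers recruitment, engagement, adherence, retention and safety, and has no acceptability row. The Recruitment section provides for logging why people decline to enter. The article describes no counterpart for withdrawal. Under Statistical analysis, missing data are described and not imputed.

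**The concern.** The people most likely to find a programme unacceptable are also the most likely to leave it. The Introduction itself expects treatment burden and long-established eating habits to make engagement difficult, so leaving is plausibly related to acceptability. An instrument given only at the end hears from those who stayed.

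What is at stake is the advice on how to change the programme. The amber cell for engagement in Table 2 points to modifications guided by the process evaluation, and the Statistical analysis section uses qualitative findings to interpret the feasibility data. If the views of leavers are absent, a decision to modify rests mainly on those for whom the programme was tolerable. Views not sought at the time of leaving may not be recoverable later.

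**Working it through.** **Step 1. Who reaches a measure under the stated schedule** (Table 1, Questionnaires, Qualitative sub-study).

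| Participant | Feedback questionnaire | Interview |
|---|---|---|
| Intervention, leaves study before week 12 | not reached | not reached |
| Intervention, leaves study between weeks 12 and 24 | not reached | only if already interviewed at week 12 |
| Routine care, leaves study before week 24 | not reached | not reached |
| Intervention, stops sessions but stays in follow-up | reached | offered |

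The first three rows are the gap; the last row is not part of it.

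**Step 2. How many could be lost.** The target is 30 participants, 20 and 10 (Sample size). Retention is green at 75% or more and amber at 51% to 74% (Table 2).

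- 23/30 = 76.7%, green, with 7 lost; 22/30 = 73.3%, amber.
- 16/30 = 53.3%, still amber, with 14 lost.

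The article does not say how losses might split between arms.

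**Step 3. Size of the possible overstatement.** The plan states no acceptability figure, so there is none to reproduce. Assume that all 20 start the intervention and that everyone who completes answers the questionnaire. Let *c* be the number of completers among the 20, *p* the share of completers who find the programme acceptable, and *q* that share among leavers. Then:

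- share over all 20 = (*p* × *c* + *q* × (20 − *c*)) / 20
- overstatement = (20 − *c*)/20 × (*p* − *q*)

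The documents give neither *p* nor *q*. With *p* assumed to be 80% (a proportion for illustration, not always a whole count):

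| Completers of 20 | Share over all 20 if *q* = 0 | If *q* = 50% | Largest overstatement |
|---|---|---|---|
| 18 (90%) | 72% | 77% | 8 points |
| 15 (75%) | 60% | 72.5% | 20 points |
| 13 (65%; all 7 green-range losses in this arm) | 52% | 69.5% | 28 points |
| 11 (55%) | 44% | 66.5% | 36 points |

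For example, with 15 completers, (0.80 × 15 + 0)/20 = 60%, and 80 − 60 = 20 points. If leavers rate the programme as completers do (*q* = *p*), the overstatement is 0. If they rate it higher, the sign reverses. Letting *p* run from 60% to 100% moves the largest overstatement from 15 to 25 points at 15 completers, and from 27 to 45 points at 11.

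**Step 4. Where the information would be used.** Amber engagement is 36% to 59%. In an arm of 20 that is 8 to 11 engaged (0.36 × 20 = 7.2; 0.59 × 20 = 11.8), so 9 to 12 not engaged. Modifying the programme depends on understanding those 9 to 12. Any of them who also leave follow-up before a scheduled measure are the ones not heard.

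**The case against.** Three stronger readings are tempting, and the documents do not support them.

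*Leavers are missed altogether.* Stopping sessions is not leaving the study: dietitian sessions and study assessments run separately, and someone who rejects the programme but attends week 24 receives the questionnaire. Interviews are offered to all intervention participants with no limit to completers, and a week-12 interview may precede a later departure. Engagement and retention count those who drop away; attendance, self-reported meal adherence and ordering data, together with the staff interviews, add indirect evidence. All of this stands and narrows the gap to those lost to the study before their scheduled point. It does not close it. These sources show that people left, or give staff views of the barriers, but they do not record the leavers' own reasons.

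*The result is biased upward, and so is the decision to progress.* The direction is likely but not certain, since people also leave for reasons unrelated to the programme. No acceptability percentage, denominator or threshold is defined, and the Table 2 classification does not use one. This stands in full.

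*Nothing is collected at withdrawal.* The article does not say so. It is a condensed account, and withdrawal procedures and recorded reasons for leaving may sit in the full protocol. Their absence here is therefore not held against the plan. The timing of the acceptability measures is different: the article states it, in several places, and ties it to weeks 12 and 24.

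**Conclusion.** The point holds as a limited weakness in the timing of measurement. For an outcome that the Introduction calls primary, the stated schedule leaves three groups without any direct acceptability measure: routine care leavers, intervention leavers before week 12, and later intervention leavers not yet interviewed. The questionnaire results are therefore likely to over-represent stayers.

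The size cannot be fixed from the documents. The ranges of 0 to 20 points at 75% arm retention and 0 to 36 points at 55% rest on an assumed 80% observed acceptability, on every completer answering, and on leavers being no more favourable than stayers. The upper ends require that no leaver found the programme acceptable. The traffic-light classification is not directly changed; what suffers is the evidence for choosing modifications. This is a cheap improvement to make before recruitment advances, not a flaw that undermines the trial.

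**What to change.** Amend Table 1, Questionnaires and Qualitative sub-study so that a short form of the existing feedback questionnaire, or the existing interview, is offered when a participant withdraws or stops sessions, without waiting for week 12 or 24.

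Report acceptability over all who started the intervention, showing non-responders as such and adding a worst-case bound that counts them as not finding it acceptable. Give the completers-only figure beside it.

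The cost is a few extra contacts and possibly a few extra £10 vouchers; the instruments already exist. Some leavers will not respond, so the picture stays incomplete but is less selective. If the full protocol already provides for this at withdrawal, it is enough to align the article's schedule with it.
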